**Table 1 Tab1:**
[figure not shown]
Schedule of trial-related activities

Abbreviations: *CT* computed tomography scan, *MRI* magnetic resonance imaging, *ECG* electrocardiogram, *NIHSS* National Institutes of Health Stroke Scale, *GCS* Glasgow Coma Scale, *mRS* modified Rankin Scale, *PRO* Patient-reported Outcome Scale of Stroke, *TCM* traditional Chinese medicine, *sICH* symptomatic intracranial hemorrhage, *AEs* adverse events, *SAEs* serious adverse events

Baseline characteristics are collected including demographics, medical history, previous medication, pre-stroke mRS, vital signs, GCS score, NIHSS score, Diagnostic Scale of Syndrome Elements in Ischemic Stroke (DSSEIS) score, time of symptom onset, time of ED arrival, time of intervention, stroke subtypes, and complications.

Independent assessors at each center, who were trained before enrollment, will be responsible for assessment including NIHSS score, GCS score, DSSEIS score, and PRO score at 48 h, 7 days, and 10 days or at discharge if earlier.

In addition, CD-ROM copies of all computed tomography (CT) and magnetic resonance imaging (MRI) scans will be collected from participating centers and assessed blindly by independent neuro-radiologists at the central trial imaging analysis center at the Institute for Cerebrovascular Disease of Beijing University of Chinese Medicine (ICVD).

### Follow-up

Independent interviewers will contact all subjects by telephone and collect follow-up information using standard Telephone Interview Forms (TIFs) at 30 days and 3 months after stroke onset. The TIF is a standard questionnaire including structured mRS, BI, locations, stroke recurrences, new-onset vascular events, self-reported information on medication use, and rehabilitation at follow-up period. All telephone interviewers, with a neurological background, will be trained to contact participants according to a standard operating procedure (SOP) before trial recruitment. All interviews will be recorded and retained.

### Data management and quality assurance

To ensure the accuracy and reliability of the data, an independent organization will be responsible for the data management. After the first participant has completed the study at each site, a site visit will be performed by the trial monitor. The monitor will review the CRFs and compare to the patient’s source medical record. Any inadequacies or errors will be reviewed with the local co-investigator and coordinator. Subsequently, site monitoring visits will be performed after every six participants enrolled at that site.

Data entry from the CRFs and TIFs will be performed in the web-based system by trained data-entry personnel using independent, dual data entry. Data are entered twice with each entry performed by a different personnel. Data-entry operators are trained to enter exactly what is recorded on the CRFs. Every structured field that is entered into the database has either a range check or internal consistency check, or both. Data-quality checks are performed by the clinical data system after the independent, dual data entry. All discrepant entries will be marked and recorded for resolution at the clinical data system. Subsequently, a trial monitor will review the two entries, resolve discrepancies, and query the entry operators and local co-investigator if necessary. All discrepancies are manually reviewed.

All study-related data and documentation will be retained by the Data Management Center at the Institute for Cerebrovascular Disease of Beijing University of Chinese Medicine (ICVD).

Several approaches were used to coordinate the different centers in order to avoid the potential heterogeneity of data. Firstly, investigators from all centers were trained to understand the clinical trial protocol and were required to comply with the standard procedure through centralized and site training before recruitment. Secondly, all assessors at each center and telephone interviewers were trained before enrollment to assure consistency among assessors. Thirdly, an independent monitoring team will be responsible for reviewing the CRFs and make sure that they comply with the medical record.

### Sample size

Based on the Third International Stroke Trial (IST-3), it is expected that 35% of the patients with AIS treated with usual care will have an independent outcome (mRS 0–2) [16]. According to previous studies [17–19], the absolute increase in the proportion of patients independent varied from 12 to 27%. Conservatively, a 12% absolute increase in the intervention group is assumed, compared with the control group. With a power of 85% and a two-sided test of a 5% type I error, a sample size of 594 would be needed. Considering the dropout rate, approximately 720 participants will be enrolled in this study.

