### Randomization

All participants will be randomly allocated to the intervention group or the control group in a 1:1 ratio. The randomization procedure will be computer- and web-based, using permuted blocks, and will be stratified for medical center. The randomization algorithm for the study will be generated and uploaded to the randomization system before recruitment. It will not be possible to know the treatment allocation before randomization. The password-protected randomization system requests a few key items of baseline data including the time of stroke onset, NIHSS score, date of birth, as well as a double check on inclusion and exclusion criteria, which are then entered with the computer keypad or tablet computer. When the data have been entered and checked, the computer will generate the treatment allocation. Participants who do not meet the criteria will be excluded by the system automatically and will not be randomized.

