### Statistical analyses

Statistical analysis will be executed on the intention-to-treat principle. All statistical tests will be performed at the 0.05 level of significance, unless otherwise specified. The Statistical Analysis System (Version 9.2, SAS Institute Inc., Cary, NC, USA) will be used to perform the statistical analyses.

Baseline characteristics will be summarized by means of simple descriptive statistics and be compared between the two treatment groups to assess covariate balance. The two-sample Student’s *t* test will be used for continuous variables and the chi-square test or Wilcoxon test will be used for categorical variables.

The primary analysis will be a comparison of the proportion of patients in each group who are independent (mRS 0, 1, and 2) at 3 months, for all those allocated XNJ versus all those allocated control using Pearson’s chi-squared test. Additional analysis will performed using the generalized Cochran-Mantel-Haenszel (CMH) test statistic to compare the distribution of mRS scores between groups.

Secondary analyses include the reduction of NIHSS, the total score and score in four dimensions of PRO, incidence of cardiovascular events, mortality, the proportion of BI scores ≥ 90, END, and sICH. Secondary outcome analyses will be carried out according to standard statistical principles for comparison of parametric or non-parametric distributions as appropriate. Multivariable regression analysis will be used to adjust for chance imbalances in the main prognostic variables between groups, such as age, stroke severity (NIHSS score), time since onset, ischemic stroke subtype, whether atrial fibrillation, and whether diabetes mellitus.

Pre-defined subgroup analyses will be performed of the effect of treatment at 3 months, subdivided by the following baseline features: time since onset, age, gender, clinical stroke syndrome using the Trial of Org 10172 in Acute Stroke Treatment (TOAST) classification, stroke severity according to the NIHSS, blood pressure at randomization, and TCM syndrome (Zheng, a key concept in TCM) [20].

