### Missing data

Missing data may cause seriously compromised inferences to scientific credibility of causal conclusions from clinical trials. Missing data are mainly caused by discontinued treatment due to adverse events, lack of tolerability, lack of efficacy, or simple inconvenience. To limit the extent of missing data, several approaches are taken according to previous experience [21]. When the assigned treatment is discontinued, efforts will be made to obtain the participant’s consent for the collection of data on treatments and outcomes. Patients with no data available after randomization will have worst-case values assigned for the 3-month data point (e.g., mRS = 6, BI = 0).

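### The increase from 594 to about 720 treats dropouts as leaving the analysis, but the plan keeps at least some as failures; power would be about 80%, not 85%, if the whole implied 17.5% were scored mRS = 6

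*Protocol article*

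**What the plan says.** All of this is in the protocol article.

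- **Sample size.** The control rate of independence (mRS 0 to 2) is taken as 35%. For the effect: "Conservatively, a 12% absolute increase in the intervention group is assumed, compared with the control group". Then: "With a power of 85% and a two-sided test of a 5% type I error, a sample size of 594 would be needed". And: "Considering the dropout rate, approximately 720 participants will be enrolled in this study". No dropout rate is given.
- **Randomization.** Allocation is 1:1, so 720 means 360 per arm.
- **Statistical analyses.** "Statistical analysis will be executed on the intention-to-treat principle". The primary comparison is a Pearson chi-squared test of the proportion independent at 3 months, "for all those allocated XNJ versus all those allocated control".
- **Missing data.** "Patients with no data available after randomization will have worst-case values assigned for the 3-month data point", with mRS = 6 and a Barthel Index of 0 as the examples. The section gives no value for a patient who has in-hospital or 30-day data but no 3-month mRS.

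**The concern.** Dividing a required sample size by one minus the dropout rate is the right correction when dropouts disappear from the analysis and the remaining patients keep the assumed event rates. It is not enough when dropouts stay in the denominator and count as failures. In that case no numbers are lost, but both rates are pulled towards zero and the difference between the arms shrinks in proportion. The Sample size section allows for lost numbers and makes no allowance for a diluted effect.

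The stated 85% is the figure against which a null result would be read. If the effective power is nearer 80%, a true 12-point benefit would be missed about one time in five rather than about one time in seven (15%).

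**Working it through.** **Inputs from the protocol article.** Control rate 0.35; intervention rate 0.35 + 0.12 = 0.47; two-sided alpha 0.05 (z = 1.960); power 0.85 (z = 1.036); 594 evaluable; about 720 enrolled, 360 per arm.

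**Step 1: reproduce 594.** Unpooled normal approximation, per arm:

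n = (1.960 + 1.036)² × (0.35 × 0.65 + 0.47 × 0.53) / 0.12² = 8.978 × 0.4766 / 0.0144 = 297.2

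The total is 594.3, which agrees with 594. The pooled formula gives 602. By the pooled formula, 297 per arm has 84.6% power (84.6% by simulation of the chi-squared test too), so the stated 85% is sound for 594 complete cases.

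**Step 2: the implied allowance.** 1 − 594/720 = 0.175, that is 126 patients. This is inferred, and 720 is given as approximate. Nearby choices give 594/0.85 = 699, 594 × 1.2 = 713 and 594/0.80 = 743.

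**Step 3: all of the implied 17.5% scored mRS = 6.** Assume the same share in both arms, unrelated to outcome.

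- Control: 0.35 × 0.825 = 0.289
- Intervention: 0.47 × 0.825 = 0.388
- Difference: 0.12 × 0.825 = 0.099

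Power with 360 per arm, where the mean rate is 0.338:

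- standard error under the null: √(2 × 0.338 × 0.662 / 360) = 0.0353
- standard error under the alternative: √((0.289 × 0.711 + 0.388 × 0.612) / 360) = 0.0351
- power = Φ((0.099 − 1.960 × 0.0353) / 0.0351) = Φ(0.85) = 80.3%

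Simulation of the chi-squared test gives 80.4%. For scale only, 85% power at these rates would take about 818 patients.

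**Step 4: other shares scored as failures, 720 patients, same assumptions.**

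| Share missing and scored mRS = 6 | Rates | Power |
|---|---|---|
| 0% | 35.0% vs 47.0% | 90.7% |
| 5% | 33.3% vs 44.7% | 88.2% |
| 10% | 31.5% vs 42.3% | 85.3% |
| 12.5% | 30.6% vs 41.1% | 83.7% |
| 15% | 29.8% vs 40.0% | 82.0% |
| 17.5% | 28.9% vs 38.8% | 80.3% |
| 20% | 28.0% vs 37.6% | 78.5% |

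Power crosses 85% at about 10.5%.

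**Step 5: 17.5% missing, only part imputed, the rest excluded.** If a fraction f of the missing is imputed, n per arm = 297 + 63f and each rate is multiplied by 297/n.

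| Part of the 17.5% that is imputed | n per arm | Power |
|---|---|---|
| None | 297 | 84.6% |
| 3 percentage points | 308 | 83.8% |
| One quarter | 313 | 83.4% |
| One half | 328.5 | 82.2% |
| Three quarters | 344 | 81.2% |
| All | 360 | 80.3% |

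**Step 6: dependence on the two assumptions, all missing imputed.**

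- Unequal by arm: 15% missing on control and 20% on XNJ gives 29.8% vs 37.6% and power of about 61%. The reverse gives 28.0% vs 40.0% and about 92%.
- Related to outcome: suppose the missing 17.5% would have been independent half as often as the full cohort. The rates are then 0.35 × (1 − 0.0875) = 31.9% and 0.47 × (1 − 0.0875) = 42.9%, and power is about 86%.

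**The case against.** The strongest objection concerns the scope of the imputation rule. Read literally, it covers only patients with no data at all after randomization. Patients are assessed at 48 h, 7 days and 10 days or discharge, and telephoned at 30 days, so many who lack a 3-month mRS will have some data. Their handling is not stated in the article and may sit in a fuller document. If only 3 percentage points of the 17.5% fell under the rule and the rest were excluded, power would be 83.8% against 84.6% for 594 complete cases, a loss of about one point. This stands. It is why the 80% figure can be given only as a conditional result. Exclusion, however, does not sit easily with a comparison of all those allocated.

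Second, the protocol states no dropout rate. The 17.5% is inferred, and a planning allowance is often a cautious upper margin. With 10% or fewer imputed, 720 patients meet the stated power. This also stands.

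Third, the dilution assumes that missing patients would have done as well as the others. If they would have done markedly worse, less is lost, and Step 6 shows power of about 86% in one such case. This stands as an assumption to be named.

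It can also be said that adding patients for dropout alongside an intention-to-treat analysis is common, and that 594 is correct. Both are true, but neither makes the 720 consistent with an analysis that scores dropouts as failures.

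A reader might infer that the trial simply lacks its stated power, or that the protocol scores every dropout as a failure. The documents support neither: the rule is narrower than that, and the expected dropout is not given.

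**Conclusion.** The concern holds in conditional form. The enrolment target was reached as if dropouts leave the analysis, while the analysis includes all allocated patients and gives mRS = 6 to at least some of those without data.

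At the allowance that the sizing itself implies, power lies between about 80% (all imputed) and just under 85% (none imputed, all excluded). The most that is lost on these assumptions is about five points. The stated 85% is met if missing outcomes scored as failures stay at or below about 10.5%.

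These figures rest on the protocol's 35% and 47%, on missingness equal in both arms, and on missingness unrelated to outcome. Confidence in the arithmetic is high. Confidence that power actually falls short is moderate, because it depends on a dropout rate and an imputation scope that the article does not fix.

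**What to change.** No further enrolment is needed. In the Sample size and Missing data sections:

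1. State the dropout rate behind 720.
2. Say whether mRS = 6 is assigned to every patient without a 3-month mRS or only to those with no post-randomization data. If the latter, say how the remaining patients enter the primary comparison.
3. Restate the power for that analysis, computed on the diluted rates. If the rule covers every missing 3-month mRS, give either about 80% with 17.5% imputed, or 85% on condition that imputed outcomes stay at or below about 10%. If it is narrower, use the matching value from Step 5.
4. Name the assumptions of equal and outcome-independent missingness.

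The cost is a few sentences and, under the broader rule, a slightly less favourable power figure. The 10% condition would also give the trial a concrete follow-up target.

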### Statistical analyses

Statistical analysis will be executed on the intention-to-treat principle. All statistical tests will be performed at the 0.05 level of significance, unless otherwise specified. The Statistical Analysis System (Version 9.2, SAS Institute Inc., Cary, NC, USA) will be used to perform the statistical analyses.

Baseline characteristics will be summarized by means of simple descriptive statistics and be compared between the two treatment groups to assess covariate balance. The two-sample Student’s *t* test will be used for continuous variables and the chi-square test or Wilcoxon test will be used for categorical variables.

The primary analysis will be a comparison of the proportion of patients in each group who are independent (mRS 0, 1, and 2) at 3 months, for all those allocated XNJ versus all those allocated control using Pearson’s chi-squared test. Additional analysis will performed using the generalized Cochran-Mantel-Haenszel (CMH) test statistic to compare the distribution of mRS scores between groups.

Secondary analyses include the reduction of NIHSS, the total score and score in four dimensions of PRO, incidence of cardiovascular events, mortality, the proportion of BI scores ≥ 90, END, and sICH. Secondary outcome analyses will be carried out according to standard statistical principles for comparison of parametric or non-parametric distributions as appropriate. Multivariable regression analysis will be used to adjust for chance imbalances in the main prognostic variables between groups, such as age, stroke severity (NIHSS score), time since onset, ischemic stroke subtype, whether atrial fibrillation, and whether diabetes mellitus.

Pre-defined subgroup analyses will be performed of the effect of treatment at 3 months, subdivided by the following baseline features: time since onset, age, gender, clinical stroke syndrome using the Trial of Org 10172 in Acute Stroke Treatment (TOAST) classification, stroke severity according to the NIHSS, blood pressure at randomization, and TCM syndrome (Zheng, a key concept in TCM) [20].

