### Outcome measures

#### Primary outcome

The primary outcome is the proportion of patients independent at 3 months after stroke onset defined by a mRS score of 0, 1, or 2. Scores on this scale range from 0 to 6, with higher scores indicating greater disability [12].

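### The unadjusted chi-squared primary test is valid, but it gives up power by leaving out prognostic variables recorded before allocation and the centre stratification

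*Protocol article*

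**What the plan says.** The primary outcome is binary: "the proportion of patients independent at 3 months after stroke onset defined by a mRS score of 0, 1, or 2" (Primary outcome). The Statistical analyses section compares the two arms "for all those allocated XNJ versus all those allocated control using Pearson’s chi-squared test" and names neither a stratum nor a covariate. A generalized CMH test on the full mRS distribution is additional, also with no stratum named.

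Allocation is made "using permuted blocks, and will be stratified for medical center" (Randomization), across 30 hospitals (Recruitment). The same Randomization section has onset time, NIHSS score and date of birth entered before the system releases an allocation.

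Adjustment comes later, in the paragraph on secondary analyses: "Multivariable regression analysis will be used to adjust for chance imbalances in the main prognostic variables between groups". Six variables follow as examples: age, NIHSS, time since onset, stroke subtype, atrial fibrillation and diabetes. Centre is not among them, and the list is not closed. Separately, baseline characteristics are to "be compared between the two treatment groups to assess covariate balance", using t, chi-squared or Wilcoxon tests.

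**The concern.** The only factor used to structure the randomization plays no part in the analysis text. Three variables that the plan regards as prognostic, and that are known for every randomized patient, are left out of the test that decides the trial. With a binary outcome, leaving out strong predictors does not bias the test, but it costs power. At stake is a better chance of detecting the assumed effect from the same patients and the same data.

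The second issue is how the adjusted analysis is described. Presenting regression as a remedy for chance imbalance, with an open list of examples, leaves room to choose the covariates after the data have been seen. In an open-label trial that room is better closed.

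**Working it through.** **Inputs from the Sample size section.** "it is expected that 35% of the patients with AIS treated with usual care will have an independent outcome"; "a 12% absolute increase in the intervention group is assumed, compared with the control group", which gives 47% with XNJ; "With a power of 85% and a two-sided test of a 5% type I error, a sample size of 594 would be needed". Allocation is 1:1.

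**Step 1: reproduce 594.** Take z(0.975) = 1.960, z(0.85) = 1.036, difference 0.12 and mean rate 0.41.

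- Pooled variance: n per arm = [1.960·√(2·0.41·0.59) + 1.036·√(0.35·0.65 + 0.47·0.53)]² / 0.12² ≈ 300.1, so 301 per arm, 602 in total.
- Unpooled variance: n per arm = (0.2275 + 0.2491)·(1.960 + 1.036)² / 0.0144 ≈ 297.2, so 298 per arm, 596 in total (594 if rounded to 297).
- Power at 297 per arm is 84.6%.

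The stated 594 is therefore that of an unadjusted two-proportion test, and the planned test and the planned size agree.

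**Step 2: power with and without adjustment.** The protocol gives no figure for centre variation or covariate strength, so both are assumed over a range. Setting: 30 equal centres, permuted blocks of 4 within centre, a logistic outcome model with marginal rates of 35% and 47%, and N = 600. The SDs are on the logit scale. The rows with centre SD 0.3 use 2,000 simulated trials each, with score AUC 0.71, 0.76 and 0.82. The other rows use 3,000 each. Adjusted here means a logistic regression on treatment and one prognostic score, without centre.

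| Centre SD | Score SD | Chi-squared | CMH by centre | Adjusted |
|---|---|---|---|---|
| 0.3 | 0.8 | 83.8% | 83.8% | 88.6% |
| 0.3 | 1.1 | 85.4% | 85.5% | 90.9% |
| 0.3 | 1.5 | 85.9% | 86.0% | 94.3% |
| 0 | 0 | 85.6% | 85.6% | 85.3% |
| 0 | 1.0 | 83.2% | 83.2% | 88.9% |
| 0 | 1.5 | 85.7% | 85.6% | 94.5% |
| 0.5 | 0 | 85.6% | 86.5% | 85.6% |
| 0.5 | 1.0 | 84.7% | 85.2% | 89.5% |
| 0.5 | 1.5 | 85.9% | 86.1% | 94.9% |
| 1.0 | 0 | 88.0% | 91.4% | 87.8% |
| 1.0 | 1.0 | 86.2% | 88.4% | 90.3% |
| 1.0 | 1.5 | 87.8% | 89.9% | 94.8% |

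The Monte Carlo standard error is about √(0.85·0.15/2000) = 0.8 points, or 0.65 points with 3,000 trials. Much of the spread in the chi-squared column up to centre SD 0.5 is therefore noise around the 85% target. A further run with a weak score gave about 87.5% adjusted.

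- At centre SD 0.3 the gain from the score is 88.6 − 83.8 = 4.8, 90.9 − 85.4 = 5.5 and 94.3 − 85.9 = 8.4 points.
- The gain from centre alone is 0–1 point up to centre SD 0.5. At centre SD 1.0 it is 2–3 points.
- A covariate that predicts nothing (score SD 0) costs essentially nothing.

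**Step 3: type I error.** In 4,000 trials per setting at N = 720 with no effect, the chi-squared test rejects in about 5% for centre SD 0–0.5. At centre SD 1.0 it rejects in 2.7–4.4%. CMH by centre stays at about 4.2–5.3% throughout. Ignoring centre never inflates the error; at worst it makes the test conservative.

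**The case against.** The strongest reply is that nothing here is wrong. The endpoint is a proportion, the trial was sized for a two-proportion test, and the chi-squared test is that test. It controls type I error and delivers the planned power, and adjustment would only exceed the target. The gain also depends on covariate strength that no section documents, and eligibility (NIHSS 5–20, age 35–80, little or no prior disability) narrows the prognostic spread, so the top of the range may be optimistic. Replacing a primary analysis during recruitment is a formal change. All of this stands, and it limits the point to an improvement.

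Three stronger readings that a reader might infer do not stand:

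- **That baseline tests decide which covariates enter.** No sentence says so. The regression is promised without condition, and six variables are named. The text does not exclude such selection, which is a weaker statement.
- **That a disagreement between the chi-squared and adjusted results would have no agreed resolution.** The chi-squared comparison is called the primary analysis and the regression sits among the secondary ones, so the order is explicit.
- **That the power comparison can simply be moved to 720 patients.** The chi-squared test has 90.7% power at 360 per arm, but only if all 720 contribute. The increase from 594 is for dropout: 594/720 = 0.825, an implied 17.5%.

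**Conclusion.** The point holds as a recommendation to improve efficiency and tighten pre-specification. The primary test is valid and 594 is reproduced to within rounding and choice of formula. Neither an inflated error rate nor a wrong sample size can be inferred.

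What is forgone is roughly 3 to 9 percentage points of power at about 600 patients: from 84–86% to about 87–90% with a weak to moderate prognostic score, and to about 95% with a strong one. This rests on assumed covariate strength, a correctly specified logistic model with one score standing in for NIHSS, age and time since onset, and equal centres. Centre by itself matters little unless centres differ by about 1 on the logit scale, for which the protocol gives no evidence. The open list and the imbalance wording are a lesser weakness, removed by the same change.

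**What to change.** Before database lock, and while the statistician is still unaware of allocation as the Blinding section provides, amend the Statistical analyses section as follows:

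- Make the primary analysis a logistic regression of mRS 0–2 at 3 months on treatment, with baseline NIHSS, age and time since onset as a closed covariate list and centre as a random effect. At about 720/30 = 24 patients per centre, a random effect is preferable to 30 fixed effects.
- State that these covariates are used whatever imbalance is seen and that the baseline comparisons play no part in choosing them.
- Report the standardized risk difference with its 95% CI.
- Keep the Pearson chi-squared test as a sensitivity analysis.
- Stratify the CMH test on the mRS distribution by centre.

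No extra patients or data are needed. All three covariates come from items entered before allocation, so no randomized patient is lost through a missing covariate, and the sample size need not rise. The costs are a plan amendment during recruitment, some dependence on the model, and an odds ratio that becomes conditional on the covariates and so needs the standardized risk difference beside it.
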